### Instruments

#### Caregiver Burden Scale

The Caregiver Burden Scale was adapted and validated to the Brazilian context in 1998, obtaining intra and interobserver reproducibility coefficients of 0.87 and 0.92, respectively [32]. This scale has been used in research to evaluate the caregiver’s burden of caring for stroke patients. It has 22 items divided into five dimensions: general tension, isolation, deception, emotional involvement and environment. It addresses important areas for caregivers such as health, mental well-being, personal relationships, physical burden, social support, finances and the environment [36]. To these questions, answers from 1 to 4 can be attributed, being: 1 – not at all; 2 – rarely; 3 – sometimes and 4 – often. For the measurement of the caregivers burden, the total score is obtained by the arithmetic mean of the values equivalent to the answers of the 22 questions. There is no cut-off point to classify the burden [32].

### WHOQOL-BREF

The instrument World Health Organization Quality of Life-BREF (WHOQOL-BREF) has been used to assess the QofL of the caregivers. This instrument, developed by the World Health Organization (WHO) in a cross-cultural perspective, has been used in national and international research with family caregivers of older adults people with stroke [37–40]. It consists in 26 questions and has two general questions about QofL. It has four domains: “Physical,” “Psychological,” “Social relations” and “Environmental” and there is no cut-off point for the worst or better QofL. The instrument provides a global score and for each of the four domains. The higher the score, the better the perception of QofL [41].

For caregivers aged older than 60 years, in addition to the WHOQOL-BREF, the WHOQOL-OLD module will be applied to evaluate the QofL of the older adults [42]. The OLD has six facets of four items each: “Sensory Abilities,” “Autonomy,” “Past, Present and Future Activities,” “Social Participation,” “Death and Dying” and “Intimacy.” The WHOQOL-BREF and the module OLD were validated for use in Brazil, presenting a Cronbach’s alpha of 0.91 and 0.885, respectively [33, 34].

### Functional Independence Measure

The Functional Independence Measure (FIM) verifies the level of independence of the older adults and was developed in the 1980s by a North American task force organized by the American Academy of Physical Medicine and Rehabilitation and the American Congress of Rehabilitation Medicine [43]. This is an instrument that presents the incorporation of the cognitive evaluation and is being widely used internationally [44].

The scale was translated into Brazilian Portuguese in 2000, obtaining an intraclass coefficient equal to 0.97 [43], and underwent a validation process in 2004 [35]. It is composed of 18 categories, grouped into six dimensions, referring to the motor and cognitive domains: self-care, sphincter control, transfers, locomotion, communication and social cognition. Each task is classified by the score of seven levels (1: total dependency; 2: maximum dependency; 3: moderate dependency; 4: minimal dependency; 5: supervision, stimulation or preparation; 6: independence modified and 7: complete independence) [43]. The total FIM score is obtained by adding the scores of each dimension, the minimum being 18 and the maximum of 126 points [35].

### Other outcomes

Hospital readmissions: yes or no?

Use of services: information will be collected by a questionnaire prepared for the study related to the health care services used by the stroke survivors and their caregivers, as well as the reason for using the services. The services expected to be commonly used by stroke survivors and family caregivers are services from the health public system such as primary health care centers, appointments with nurses and physicians, pharmacies and emergency departments. Furthermore, they may use services from the private health services such as hospitals and appointments with physicians.

### Statistical methods

#### Sample size

The calculation of the sample was estimated by the burden outcome and was based on a study that demonstrated a difference between the caregiver’s burden and an improvement in their QofL after an educational intervention [5]. Considering a confidence level of 0.95, a statistical power of 0.80, a minimum effect size of 0.9 standard deviations between the groups regarding the burden and QofL, and a sample loss of 20%, the sample was calculated in 48 patients. There was a fair division between the two groups, with 24 patients in the IG and 24 patients in the CG. The statistical calculation was performed by the program WinPepi version 11.32 [45].

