**Methods:**

A randomized clinical trial with 48 family caregivers of stroke survivors will be recruited and divided into two groups: 24 in the intervention group and 24 in the control group. The intervention will consist of the systematic follow-up by nurses who will perform three home visits over a period of 1 month. The control group will not receive the visits and will have the usual care guidelines of the health services. Primary outcomes: burden and quality of life of the caregiver. Secondary outcomes: functional capacity and readmissions of the stroke survivors; the use of health services of the stroke survivors and their family caregivers. Outcomes will be measured 2 months after discharge. The project was approved in April 2016.

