### Data analysis

The analysis will be performed by intention-to-treat, where data from all participants (stroke survivors and their family caregivers) will be used regardless of the time they participated in the study [46]. Quantitative variables will be expressed as means and standard deviations or median and interquartile range. The Shapiro-Wilk test will be used to assess the distributions of the continuous outcomes. For the qualitative variables, absolute and relative frequencies will be presented. Student’s *t* test, the Mann-Whitney *U* test, Pearson’s chi-square test or Fisher’s exact test according to normality will be used to compare the groups. The linear regression model (quantitative outcomes) and the Poisson regression analysis (qualitative outcomes) will be applied, considering a *p* value of less than 0.20 in the bivariate analysis. A *p* < 0.05 will be considered. The Statistical Package for Social Sciences (SPSS) version 21.0 will be used for analysis.

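### With 48 randomised and the stated 20% loss, a two-sided t test has about 77–78% power for 0.9 SD, slightly below the stated 80% (minor)

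*Protocol article*

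**What the plan says.** The Sample size section lists its inputs as "Considering a confidence level of 0.95, a statistical power of 0.80", then "a minimum effect size of 0.9 standard deviations between the groups regarding the burden and QofL", and closes with "a sample loss of 20%, the sample was calculated in 48 patients". The split is equal, "with 24 patients in the IG and 24 patients in the CG", and the Abstract repeats it. WinPepi is named as the software. The section does not give the number before loss, whether the test is one- or two-sided, the formula, or how the loss was added.

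The Data analysis section says that Student's t test, the Mann-Whitney U test or a test for proportions, chosen by distribution, will compare the groups. Regression models follow. The significance criterion is "A *p* < 0.05 will be considered", again without a side.

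**The concern.** The sentence tells the reader that 48 participants give 80% power for 0.9 SD even if one in five is lost. Two features suggest that it falls a little short. First, 48 is exactly 40 × 1.2, whereas allowing for a 20% loss means dividing by 0.80, which gives 50. Second, at about 20 per arm the normal approximation and the t test differ by around 2 points of power, and the named test is the t test. If the result is null, readers will judge it against the stated power, so that figure should be the one the trial has at its own assumed loss.

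**Working it through.** **Inputs.** Difference 0.9 SD, power 0.80, loss 20% and 24 + 24 enrolled, all from the Sample size section. Alpha is 0.05, from the 0.95 confidence level. Two-sided testing is an assumption. A one-sided test needs 16 per arm, and 16 / 0.80 = 20 per arm, or 40 in total, which does not reproduce 48.

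**Reproducing the plan's figure (normal approximation).**

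- Per arm before loss: 2 × (1.96 + 0.8416)² / 0.9² = 19.38, rounded up to 20, so 40 in total.
- Loss added by multiplying: 20 × 1.2 = 24 per arm, 48 in total.
- Loss added by dividing the rounded number: 20 / 0.80 = 25 per arm, 50 in total.
- Loss added by dividing the unrounded number: 19.38 / 0.80 = 24.2 per arm, 48.45 in total, which becomes 48 if rounded to the nearest whole number.

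The first and third routes both arrive at 48.

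**Same inputs with the t test (noncentral t).** 80% power needs 20.39, so 21 completers per arm. Then 21 / 0.80 = 26.25, so 27 per arm, or 54 in total with equal arms. This route does not give 48, so the plan's figure rests on the normal approximation.

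**Power after loss.** 48 × 0.80 = 38.4 completers, or 19.2 per arm. For 19 per arm the noncentrality is 0.9 × √(19/2) = 2.77 on 36 degrees of freedom. Two-sided 5% power for 0.9 SD:

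| Completers | Normal approximation | t test |
|---|---|---|
| 24 + 24 (no loss) | 87.7% | 86.3% |
| 21 + 21 | 83.1% | 81.2% |
| 20 + 20 | 81.2% | 79.2% |
| 19 + 20 | 80.2% | 78.1% |
| 19.2 + 19.2 | 79.6% | 77.5% |
| 19 + 19 | 79.2% | 77.0% |

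At 19 per arm, the difference that the t test detects with 80% power is 0.934 SD.

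**Splitting the gap.** Start from 20 completers per arm on the normal approximation, 81.2%.

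- Having 19 rather than 20 per arm lowers this to 79.2%, a drop of 2.0 points.
- Using the t distribution lowers it again to 77.0%, a drop of 2.2 points.

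Neither part explains the result alone. With 50 enrolled, 20 per arm would remain and the t test would still have only 79.2%.

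**Loss that 48 can absorb.** Keeping 40 completers allows 8 losses: 8 / 48 = 16.7%.

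**The case against.** The strongest reply is that the plan's sum is consistent with itself. On the formula that reproduces 48, power after 20% loss is 79.2% to 80.2%, which most readers would call 80%. Using the normal approximation to size a trial is common, and the Sample size section does not claim an exact t calculation. The loss allowance is worth only two participants (50 against 48), and both the 20% loss and the 0.9 SD are round planning values. The analysis is also not tied to an unadjusted t test, since Mann-Whitney and linear regression are listed too.

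Much of this stands, and it is why the point is minor. It does not remove the point. The comparison will be made with a t test or a rank test, not with a z test, and for the t test the power at the plan's own loss is below 80%. For normal data the Mann-Whitney test would do slightly worse: about 75% at 19 per arm, using its relative efficiency of 0.955. What a baseline-adjusted regression would gain depends on a correlation that the article does not give.

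A reader might go further and infer that the authors multiplied by 1.2 where they should have divided by 0.80. The article does not support that as a finding. It gives no number before loss, and dividing the unrounded size also leads to 48. Nor would such an error account for the whole shortfall, because about half of the drop comes from the approximation.

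**Conclusion.** Wrong as written, but minor. For the t test, 48 participants with 20% loss give about 77–78% power for 0.9 SD, against the stated 80%. The detectable difference at 80% power is about 0.93 SD, not 0.90. The shortfall is 2 to 3 points and does not threaten the design.

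The result assumes a two-sided 5% test, loss of exactly 20%, and completers split about equally. Simple randomisation does not guarantee an equal split, but mild imbalance matters little: 18 + 20 completers give 76.9%. If the test were one-sided, power at 19 per arm would be 85.9%, but that reading does not lead to 48. How the loss was added remains unknown.

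**What to change.** Keep 48 and restate what it delivers, for example: *With 20% loss (about 38 completers), a two-sided 5% t test has about 77% power for a difference of 0.9 SD and 80% power for 0.93 SD; with no loss, power for 0.9 SD is 86%.* In the same place, state the sidedness, the number before loss and how the loss was added. If power for a baseline-adjusted analysis is also quoted, give the correlation it assumes.

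The cost is a sentence or two. Recruitment, which the Trial status section shows was already under way, does not change. The one drawback is that the stated power becomes slightly less favourable.

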### Data analysis

The analysis will be performed by intention-to-treat, where data from all participants (stroke survivors and their family caregivers) will be used regardless of the time they participated in the study [46]. Quantitative variables will be expressed as means and standard deviations or median and interquartile range. The Shapiro-Wilk test will be used to assess the distributions of the continuous outcomes. For the qualitative variables, absolute and relative frequencies will be presented. Student’s *t* test, the Mann-Whitney *U* test, Pearson’s chi-square test or Fisher’s exact test according to normality will be used to compare the groups. The linear regression model (quantitative outcomes) and the Poisson regression analysis (qualitative outcomes) will be applied, considering a *p* value of less than 0.20 in the bivariate analysis. A *p* < 0.05 will be considered. The Statistical Package for Social Sciences (SPSS) version 21.0 will be used for analysis.

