### Recruitment and randomization

The stroke survivors and their family caregivers will be selected during the hospital stay at SCU-Stroke. Those who meet the inclusion criteria and are eligible will be invited to participate in SHARE. Ethical procedures will be guaranteed and participants will be able to discontinue participation at any time in the research. Participants selected will receive a HV for baseline assessment within 7 days after discharge. Participants will be picked up, selected and evaluated by research assistants, who in order to minimize bias, will be responsible for: (1) obtaining the consent of family caregivers and the stroke survivors and (2) sending the participants baseline data for randomization.

The allocation of the participants in the IG or in the CG will be through simple randomization, through a numerical list generated by the website randomization.com. This list has a numerical order, in which each number is already assigned to one of the groups randomly. Thereafter, patients are given a number and their designation as they are included in the study. Randomization will occur after the baseline evaluation of stroke survivors and family caregivers, and will be performed by a trained research assistant who is not involved in the evaluation of the participants nor involved in the SHARE intervention.

The CG will receive conventional care, and the IG will receive the SHARE intervention. The assistant responsible for randomization will inform the interventional nurses which patients are assigned to the IG. The final evaluation of all participants will be performed by the same research assistants in the initial assessment 60 days after the date of the patient’s discharge from the hospital. The logistics of the study are presented in Fig. 2. Regarding the blindness, the trial will have outcomes obtained from blinded evaluators. Study participants will not be blind to the intervention.

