### Data collection and outcomes

#### Primary and secondary outcomes

The primary outcomes will be: the caregiver’s burden and QofL, as measured by the Caregiver Burden Scale and by the World Health Organization Quality of Life–BREF (WHOQOL-BREF)_ and the World Health Organization Quality of Life (for caregivers aged over 60 years) (WHOQOL-OLD) [32–34]. Secondary outcomes: functional capacity measured by Functional Independence Measure (FIM) [35]; the hospital readmission of the stroke survivors and the use of health care services by participants after the stroke episode. Primary outcomes and functional capacity will be measured within 1 week after discharge and 2 months after discharge. The outcomes of hospital readmission and use of health services will be evaluated 60 days after discharge (Table 1).

**Table 1 Tab1:** Outcomes and time of data collection: stroke survivors and their family caregivers

Outcome and instrument	Family caregiver vs. stroke survivors	Data collection time	
		T0 (7 days)	T1 (60 days)
Primary outcomes			
Caregiver Burden Scale	Family caregiver	X	X
World Health Organization Quality of Life (WHOQOL-BREF and -OLD)	Family caregiver	X	X
Secondary outcomes			
Functional Independence Measure (FIM)	stroke survivor	X	X
Hospital readmission (yes/no)	stroke survivor		X
Use of health care services	Family caregiver and stroke survivor		X

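### Each scale's baseline score, taken before randomisation, is not secured as a covariate: the group tests are unadjusted and the regression leaves adjustment to a p < 0.20 screen

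*Protocol article*

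**What the plan says.** Under Primary and secondary outcomes, the protocol article states: "Primary outcomes and functional capacity will be measured within 1 week after discharge and 2 months after discharge". Table 1 there marks burden, WHOQOL (BREF and OLD) and FIM at both T0 (7 days) and T1 (60 days). Burden and quality of life are the primary outcomes, measured on the caregiver. FIM is secondary, measured on the stroke survivor.

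Recruitment and randomization fixes the order: "Randomization will occur after the baseline evaluation of stroke survivors and family caregivers". Allocation is by simple randomisation, with no stratification described.

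Data analysis lists Student's t, Mann-Whitney, chi-square and Fisher tests, which "according to normality will be used to compare the groups". None of these takes a covariate. The next sentence adds linear regression for quantitative outcomes and Poisson regression for qualitative ones, applied with a bivariate threshold of p < 0.20. The section does not say which of the two analyses decides the result, what the threshold screens against, or how the T0 score is treated.

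Sample size assumes "a minimum effect size of 0.9 standard deviations between the groups regarding the burden and QofL". The total of 48, split 24 per arm, includes an allowance of 20% for dropout.

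**The concern.** A score on the same scale, taken before randomisation, is usually the best predictor of the follow-up score. Adjusting for it removes variation from the treatment comparison at no cost in data. Here it is collected on every participant before allocation, so it is a legitimate covariate for each continuous outcome.

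The plan does not make sure it is used. The group tests ignore it, and the regression admits covariates through a screen whose target is not stated. The final estimate may therefore be adjusted or unadjusted depending on the observed data and on how a reader interprets one clause. In a trial of 48 dyads planned on an effect as large as 0.9 SD, the precision at stake can matter.

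**Working it through.** **Inputs.** From Sample size: confidence level 0.95 (taken as two-sided 5%, since sidedness is not stated), power 0.80, effect 0.9 SD, loss 20%, 24 per arm. Assumed, because the article gives no figure: a T0-T1 correlation r of 0.3, 0.5 or 0.7.

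**1. The plan's own figure.** n per arm = 2(1.960 + 0.842)² / 0.9² = 19.4, rounded up to 20. Two arms give 40, and 40 × 1.2 = 48, as stated. (Dividing by 0.8 instead gives 50.) No baseline correlation enters, so the design calculation is an unadjusted comparison of two means.

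**2. Completers.** 24 × 0.8 = 19.2, taken as 19 per arm.

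**3. Unadjusted t test.** SE = √(2/19) = 0.324 SD. Noncentrality = 0.9 / 0.324 = 2.77 on 36 df. Power = 0.77.

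**4. Fixed adjustment for T0.** SE = √(1 − r²) × √(2/19) × √(1 + 1/34) on 35 df. The last factor is the approximate price of estimating one covariate.
- r = 0.3: SE 0.314, noncentrality 2.87, power 0.80
- r = 0.5: SE 0.285, noncentrality 3.16, power 0.87
- r = 0.7: SE 0.235, noncentrality 3.83, power 0.96

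Set against 0.324, the standard error falls by about 3%, 12% and 27%.

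**5. The screened regression.** This was simulated with normal T0 and T1 scores, 19 per arm, a 0.9 SD effect, and arm always kept in the model. T0 was added only when its screening p was below 0.20.

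| Analysis that decides | r = 0.3 | r = 0.5 | r = 0.7 |
|---|---|---|---|
| Unadjusted test | 77% | 77% | 77% |
| Regression, T0 screened for imbalance between arms | 77% | 80% | 83% |
| Regression, T0 screened against the outcome | 79% | 86% | 96% |
| Regression, T0 fixed in advance | 80% | 87% | 96% |

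Screened against the outcome, T0 enters in about 65%, 95% and nearly 100% of trials. Screened for imbalance, it enters in about 20% whatever the value of r.

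The imbalance screen also makes the test conservative. The unadjusted analysis is then kept just when the arms happen to agree at baseline, where its standard error is too large. At r = 0.7 the type I error falls to between 2% and 3%.

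**6. Chance imbalance.** With 24 per arm, the T0 mean difference has SE √(2/24) = 0.29 SD. A gap above 0.3 SD in either direction (0.3 / 0.29 = 1.04 standard errors) arises in about 30% of such trials. On average, r times the gap passes into the unadjusted difference.

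**The case against.** The strongest reply is that the article does plan a regression. A reader who stops at the list of tests might infer that the primary comparison is unadjusted and the baseline data are thrown away. The text does not support that: no analysis is labelled primary, and the next sentence opens a route by which T0 can enter. If that regression decides and the screen is against the outcome, a common reading of bivariate analysis, the loss is at most about 1 point. This part of the objection stands. The contrast of 77% with up to 96% applies only if the unadjusted tests decide.

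A second tempting reading is that chance imbalance biases the unadjusted result. It does not. Under randomisation the test is unbiased over repetitions, holds its 5% level, and already carries chance imbalance in its standard error. The stated sample size does not rely on adjustment either. This also stands.

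Third, covariates are often named in an analysis plan, and that plan is not shown. It may already name T0. But the article is not silent: it states both the tests and the rule for admitting covariates, and the point addresses that stated rule.

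Fourth, the tests might be meant for change from T0, since the article does not say which score is compared. That would use T0, but less efficiently. The variance factor is 2(1 − r) = 1.4, 1.0 and 0.6, against 1 − r² = 0.91, 0.75 and 0.51 for adjustment.

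**Conclusion.** The point holds as one of precision and of an unsettled rule. The T0 score of each continuous scale is available before randomisation but is not secured as a covariate, and the article does not say whether the tests or the screened regression decide.

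Compared with fixed adjustment, the loss in power at r = 0.3, 0.5 and 0.7 is:
- about 3, 10 and 19 points if the unadjusted tests decide;
- about 3, 7 and 13 points if the regression decides with an imbalance screen;
- at most about 1 point if it decides with an outcome screen.

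These figures rest on 19 completers per arm, a true effect of 0.9 SD, normal scores, arm kept in the model, and correlations that are assumed. At r = 0.3 the gain is small under any reading. The figures do not carry over to WHOQOL-OLD, which only the caregivers over 60 complete. The documents do not support a claim of bias or of an invalid test. The change is worth making, but the trial does not fail without it.

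**What to change.** For each continuous outcome, fix one linear regression of the T1 score on arm plus the T0 score of the same scale. Keep both terms regardless of the p < 0.20 screen. Apply this to burden and WHOQOL-BREF as primary outcomes, to WHOQOL-OLD in caregivers over 60, and to FIM as a secondary outcome. Report the adjusted mean difference with its 95% confidence interval, state that this analysis decides the result, and keep the t or Mann-Whitney test as a sensitivity check.

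The cost is a few sentences in Data analysis, written before any comparison between arms is seen. No new data are needed, and SPSS, the package already named, fits the model.

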### Validity and reliability/rigor

All the instruments used in this study were tested for validity and reapplicability in the Brazilian population. In addition, randomization means that there are no systematic biases regarding the subjects’ allocation, since it ensures that it is random, minimizing the influence of confounding variables. Blinding is also critical, as it controls for cointerventions and bias outcome evaluations.

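### A p < 0.20 screen sets the regression and no result is named as decisive, so the T0 scores may be left out of the model

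*Protocol article*

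**What the plan says.** The Data analysis section of the protocol article gives each outcome two analyses. The first is an unadjusted comparison by Student's t, Mann-Whitney, chi-square or Fisher: "test, Pearson’s chi-square test or Fisher’s exact test according to normality will be used to compare the groups". The second is a regression: "The linear regression model (quantitative outcomes) and the Poisson regression analysis (qualitative outcomes) will be applied", subject to a p "value of less than 0.20 in the bivariate analysis". The section does not list the variables to be screened or say what they are screened against. It also does not rank the two results.

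Elsewhere, Table 1 shows that burden, QofL and FIM are measured at T0 and T1, while readmission and service use are recorded at T1 only. Under Recruitment and randomization, the baseline assessment comes before allocation. Validity and reliability/rigor credits randomisation with "minimizing the influence of confounding variables".

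**The concern.** The rule lets the trial's own data choose the covariates, and so the treatment estimate. In a randomised trial, the reason to adjust is that a covariate predicts the outcome. The strongest predictor is usually the same scale measured before allocation. Under the stated rule, that score enters only if it happens to pass the screen.

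Two things are at stake. One is precision in a small trial that could have used the T0 score throughout. The other is that every outcome has an unadjusted and a screened p value, and the text lets either be presented as the answer.

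**Working it through.** **Inputs from the article (Sample size section).** Error rates: "Considering a confidence level of 0.95, a statistical power of 0.80". The difference to detect is 0.9 SD, for burden and for QofL alike. Attrition and total: "a sample loss of 20%, the sample was calculated in 48 patients", split as 24 per group. Two-sided testing is assumed, because sidedness is not stated.

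**Reproducing the planned size.** n per arm = 2(1.960 + 0.842)² / 0.9² = 19.4, rounded up to 20. Adding 20% gives 20 × 1.2 = 24 per arm, or 48 in total, which matches the article. Completers after 20% loss: 24 × 0.8 = 19.2, taken as 19 per arm. The plan was therefore sized for an unadjusted comparison.

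**Fixed model by formula.** Adjusting for a baseline with correlation r multiplies the SD by √(1 − r²). Power ≈ Φ(0.9 / [√(1 − r²) × √(2/19)] − 1.960), where 0.9/√(2/19) = 2.774.

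- Unadjusted: Φ(0.814) = 79% (about 77% by exact t).
- r = 0.3: 2.774/0.954 = 2.908; Φ(0.948) = 83%.
- r = 0.5: 2.774/0.866 = 3.203; Φ(1.243) = 89%.
- r = 0.7: 2.774/0.714 = 3.884; Φ(1.924) = 97%.

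**Simulation of the screen.** 19 per arm, true difference 0.9 SD, the baseline plus 8 non-prognostic candidates, 4,000 to 6,000 trials per setting. The correlation and the candidate list are assumptions. Power in %:

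| r | Fixed arm + T0 | Unadjusted t | Screen on arm difference | Screen on outcome |
|---|---|---|---|---|
| 0.3 | 80 | 77 | 71-72 | 73-74 |
| 0.5 | 87 | 77 | 73-74 | 82 |
| 0.7 | 96 | 77 | 76-77 | 94 |

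The arm-difference screen admits the baseline in about 20% of trials, as a 0.20 threshold must under randomisation. The outcome screen admits it in about 64%, 95% and 100% for the three values of r.

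**Wider settings.** Over 5 to 15 candidates, with and without other prognostic ones:

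- The fixed model has about 79-97% power.
- The arm-difference screen has about 67-82%, below the fixed model in every setting tried.
- The outcome screen can reverse sign. At r = 0.5, with two further candidates of coefficient 0.3, it gives 90% against 87% for the fixed model with 5 candidates, 88% against 87% with 10, and 84% against 87% with 15.
- The outcome screen shrinks the mean estimate from 0.90 SD to about 0.84-0.88 with 5 candidates and 0.78-0.83 with 15.

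**Two results per outcome.** With 8 non-prognostic candidates and a true 0.9 SD difference, the t test and the outcome-screened regression disagree on significance in about 13%, 14% and 20% of trials for r = 0.3, 0.5 and 0.7. Under no effect, each test alone stays near or below 5%. Counting a success when either is significant gives about 6-9% across the settings.

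**The case against.** The strongest reply is that a reader might infer that screening always costs power, and the article does not support that. If the screen is on association with the outcome and some other candidates predict it well, the screened model matches or beats adjustment for baseline alone, as the 90% against 87% result shows. The sign depends on a list that the article does not give. This part of the objection stands.

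The comparator is also a model that the article never plans. The 48 participants were sized for an unadjusted comparison, and that figure reproduces. Against that test, much of what is lost is an available gain. This stands too, and the sample size is not in question.

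Third, ranking the two analyses could be left to a fuller plan, and both the sizing and the sentence on comparing groups lean towards the unadjusted test. This stands in part: the article does not say so, and the p < 0.20 rule is a stated method rather than an omitted detail.

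Two further inferences should be resisted. The screen does not by itself inflate the type I error; the 6-9% arises only if the better result is chosen. Nor does randomisation make adjustment improper. With simple randomisation and 48 participants, chance imbalance is expected and adjustment for prognostic variables is legitimate. The objection is to the selection rule alone.

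**Conclusion.** The concern holds in a conditional form. The article fixes a data-driven rule, leaves two unranked results per outcome, and does not secure the T0 score in the model.

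If the bivariate analysis means the comparison of the groups, which is the only one the section describes, the screened regression has less power than a fixed arm-plus-T0 model. With 8 non-prognostic candidates the gap is about 8-9 points at r = 0.3, 12-14 at r = 0.5 and 19-20 at r = 0.7. If the screen is on the outcome, the firm finding is a modest pull towards zero, from 0.90 to about 0.78-0.88 SD, with no general statement possible about power. The advantage of the fixed model over the unadjusted test (about 79-97% against 77%) rests on the assumed correlation of 0.3 to 0.7.

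A reader might extend the power argument to readmission and service use. It does not reach them: they have no T0 value, and only the point about two unranked results applies.

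**What to change.** Remove the p < 0.20 screen as the basis of any main result. For burden, QofL and FIM, name linear regression on arm plus the T0 value of the same outcome as the primary analysis. Keep the unadjusted test as a sensitivity analysis and label any screened model exploratory. For readmission and service use, name one between-arm comparison as the result in advance; no gain in power is claimed there.

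This is a change of wording, to be made before the outcome data are analysed. It needs no new data, because the T0 scores are already scheduled for every participant before randomisation, and it leaves the sample size as it is.
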